## Abstract

**Background:**

Those who experience a critical illness or condition requiring admission to an intensive care unit (ICU) frequently experience physical and psychological complications as a direct result of their critical illness or condition and ICU experience. Complications, if left untreated, can affect the quality of life of survivors and impact health care resources. Explorations of potential interventions to reduce the negative impact of an ICU experience have failed to establish an evidence-based intervention.

**Objective:**

The aim of this study is to evaluate the impact of a Web-based intensive care recovery program on the mental well-being of intensive care survivors and to determine if it is a cost-effective approach.

**Methods:**

In total, 162 patients that survived an ICU experience will be recruited and randomized into 1 of 2 groups. The intervention group will receive access to the Web-based intensive care recovery program, ICUTogether, 2 weeks after discharge (n=81), and the control group will receive usual care (n=81). Mental well-being will be measured using the Hospital Anxiety and Depression Scale, The Impact of Events Scale-Revised and the 5-level 5-dimension EuroQoL at 3 time points (2 weeks, 6 months, and 12 months post discharge). Family support will be measured using the Multidimensional Scale of Perceived Social Support at 3 time points. Analysis will be conducted on an intention-to-treat basis using regression modeling. Covariates will include baseline outcome measures, study allocation (intervention or control), age, gender, length of ICU stay, APACHE III score, level of family support, and hospital readmissions. Participants’ evaluation of the mobile website will be sought at 12 months postdischarge. A cost utility analysis conducted at 12 months from a societal perspective will consider costs incurred by individuals as well as health care providers.

**Results:**

Participant recruitment is currently underway. Recruitment is anticipated to be completed by December 2020.

**Conclusions:**

This study will evaluate a novel intervention in a group of ICU survivors. The findings from this study will inform a larger study and wider debate about an appropriate intervention in this population.

**International Registered Report Identifier (IRRID):**

PRR1-10.2196/10935

## Introduction

An intensive care unit (ICU) stay is a stressful, potentially traumatic period for survivors and their families. Admission to an ICU usually means that individuals have suffered a critical illness or condition that is a threat to their lives, and they are among the most critically ill and vulnerable patients in the hospital. It is thought that the complications of a critical illness or condition are related to not only the severity of the illness but also the ICU experience [1,2]. Intensive care survivors often struggle to return to their previous role in the family and to their preillness state of health owing to prolonged physical and neuropsychological disability [3-5].

Over 172,000 people were admitted to ICUs across Australia during 2014-2015. As survival rates from ICUs have increased over the last 30 years, there has been a concomitant rise in the number of survivors, increasing the number of people who may develop chronic illness as a direct result of their ICU experience [6,7]. It has become increasingly apparent that those who survive an ICU experience and are discharged home suffer myriad physical, cognitive, and mental health impairments as a direct result of their ICU experience and critical condition [8-10]. These impairments can persist over a long period of time [4,11]. Psychological complications have been estimated to be as high as 44% of survivors at hospital discharge [1] and in some populations, they have been noted to increase during the year following hospital discharge [12].

Despite awareness of the high risk of complications post ICU discharge, support to anticipate and address physical and psychological complications is not routinely offered through existing health care services. Many survivors report being unaware of what to expect during recovery and lack knowledge of what is normal and when they need to seek help [13]. The onus to seek help post discharge sits in the hands of the survivor, and it is unknown how many “suffer in silence,” unaware if what they are experiencing is a usual part of recovery.

The purpose of this study was to determine if a Web-based intensive care recovery program improves the mental health and well-being of ICU survivors. As a mobile website, availability of the program will be unrestricted, enabling participants to access it at anytime and anywhere via a smart device. The program will enable participants to access support, advice, and guidance during their recovery post discharge from ICU.

## Methods

### Design

A parallel, prospective randomized controlled study will determine if a Web-based intensive care recovery program improves the mental health and well-being of ICU survivors. The study design for the protocol is outlined in a flow diagram in Figure 1.

### Ethical Considerations

Ethical approval was obtained from the participating study site and the university where the researchers are employed.

### Study Duration

Recruitment began in November 2018, and data collection will be completed within 2 years.

### Participants

Participants will be screened and recruited from a general 10-bed ICU within a 750-bed hospital in Metropolitan Western Australia following discharge from ICU and admission to a general ward. Eligibility criteria for Inclusion are as follows: aged 18 years and over at time of randomization, ventilation in ICU for a minimum period of 24 hours, able to speak and understand English, able to give informed consent, and access to an electronic device. Participants will be informed which group they have been randomized to immediately after providing written informed consent.

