### Randomization

Permuted block randomization will be conducted in blocks of 20 using a computer random number generator. Allocation concealment will be conducted by an independent researcher using sequentially numbered, opaque, sealed envelopes. The independent researcher will provide the researcher conducting the consent process with the sequentially numbered, sealed, opaque envelopes. Envelopes containing the treatment allocation will only be opened by the recruiting researcher on participant enrollment. Blinding of the participant to allocation status will not be possible owing to the nature of the intervention. The researchers conducting the data analysis will be blinded.

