### Intervention

Patients in the intervention group will receive access to a Web-based recovery program, ICUTogether that is accessible via smart devices and personal computers. The mobile website will provide information about health and well-being during recovery, including advice about exercise, sleep, and nutrition. Information will be provided on the recovery process, the signs and symptoms of potential complications during recovery, and when and how participants should seek professional help. Participants will be encouraged to keep a journal to promote reflection on progress over time and to explore their thoughts and feelings during their recovery. A chat room will also be available and participants will be able to post items to share with other participants in the study.

Participants will be given access to the mobile website 2 weeks following discharge from the hospital. A hard copy the self-help guide and telephone call will guide participants regarding the use of the site. If the participant is still unable to use the website, a researcher will visit their home and provide direct support with it. A demonstration of the functionality of the mobile website by a researcher will also be given at that time. The frequency of use of the website is at the discretion of the participants who will be encouraged to use the site as frequently as they wish. Each time a participant logs in, they will be prompted to complete a symptom checker that will identify material most useful to the participant at that point in time. The score from the symptom checker will be monitored and an alert notification will be sent to the researchers when the scores reach a certain level and thus gives cause for concern. Participants will receive a weekly email summarizing their participation over the previous 7 days and indicating any days they have not participated along with a prompt to continue participating.

The mobile website was developed by an external provider in collaboration with the researchers. The mobile website is being tested for ease of use and navigation properties by the researchers, clinicians, and a group of ICU survivors prior to commencement of the study.

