### Data Collection and Measures

Following the consent process, demographic data will be collected from the participants’ health records, which will include the age, gender, admission diagnosis, severity of illness (APACHE III), existing comorbidities, and ICU length of stay. Data will be collected from participants at the following 3 time points: 2 weeks post discharge, 6 months post discharge, and 12 months post discharge (primary timepoint). The following three outcome measures will be used in the study: the Hospital Anxiety and Depression Scale (HADS), the Impact of Events Scale Revised, and the 5-level 5-dimension EuroQoL. All 3 measures will be completed at each of the 3 time points. The level of family support will also be collected at these time points via the Multidimensional Scale of Perceived Support [14]. Table 1 provides a brief description of each of the outcome measures. Participants in both groups will receive the 3 surveys by email 2 weeks post discharge from the hospital to complete the first data collection time point. At the following 2 data collection time points, the 3 surveys will be sent by via email to both groups. All participants will also be contacted by telephone to provide a prompt to complete the surveys at the data collection time points.

**Table 1 table1:** Summary of outcome measures and description.

Outcome measure		Number of items	Description

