### Statistical Analysis

Data will be reported in accordance with the Consolidated Standards of Reporting Trial. Data analysis will be conducted using SPSS version 24 (IBM) and Stata SE version 15 (StataCorp). The characteristics of participants in each arm of the study will be summarized using descriptive statistics. Analysis of characteristics to determine similarity between the arms will be conducted using chi-square tests for categorical data and independent *t* tests for continuous data.

Further analysis will include stratifying the APACHE III scores into categories to determine if there is a difference in the level of severity and outcomes. The 3 outcome measures (HADS, IES, and QoL) at follow-up will be analyzed as dependent variables using regression modeling. Covariates will include baseline outcome measures, study allocation (intervention or control), age, gender, length of ICU stay, APACHE III score, and level of family support. Analysis will be conducted on an intention-to-treat basis. A subanalysis of the intervention group based on those who engaged with the mobile website compared with those who did not will also be conducted. The characteristics of people who withdraw from the study will be compared with those who remain in the study. Missing data will be addressed using multiple imputation assuming variables are missing at random. The person who completes the data analysis will be blind to participant allocation status. Summary statistics of frequency of use, time spent using the site, most frequently used elements, and time spent on each screen will be reported.

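### The self-reported baseline covariates are first collected after participants know their arm, and at the same nominal time as website access, so adjusting for them can bias the 12-month difference

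*Protocol article*

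**What the plan says.** All references are to the protocol article.

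- **Recruitment and disclosure.** Under Participants, patients are recruited "following discharge from ICU and admission to a general ward", and "Participants will be informed which group they have been randomized to immediately after providing written informed consent". Under Randomization, "Envelopes containing the treatment allocation will only be opened by the recruiting researcher on participant enrollment", and "Blinding of the participant to allocation status will not be possible owing to the nature of the intervention".
- **Data taken at consent.** Data Collection and Measures describes only health-record items at this stage (demographics, diagnosis, comorbidity, APACHE III, ICU stay). No outcome scale is listed.
- **First self-report.** The same section says: "Participants in both groups will receive the 3 surveys by email 2 weeks post discharge from the hospital". Family support is collected at the same time points. The next assessments are at 6 and 12 months, and 12 months is primary.
- **Start of the intervention.** Under Intervention: "Participants will be given access to the mobile website 2 weeks following discharge from the hospital". A printed guide and "telephone call will guide participants regarding the use of the site", with a home visit for those who still cannot use it.
- **Analysis.** Under Statistical Analysis: "Covariates will include baseline outcome measures, study allocation (intervention or control"), followed by age, gender, ICU stay, APACHE III and family support.

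**The concern.** A baseline covariate is safe to adjust for when allocation cannot have influenced it. Here every self-reported covariate is measured after randomization, by participants who know their arm. HADS and IES-R are subjective measures of distress, which hope, disappointment or a supportive call could plausibly move. Some intervention participants may also have logged in or had the set-up call before answering, because nothing in the text puts the survey first.

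If the 2-week score shifts in one arm, the regression treats that shift as a pre-existing difference and removes part of it from, or adds part of it to, the 12-month contrast. No earlier self-report exists from which such a shift could be detected. At stake is the primary estimate: the adjusted HADS difference at 12 months.

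**Working it through.** **1. Which measurement is the baseline.** Statistical Analysis does not date the baseline. The assessments are at 2 weeks, 6 months and 12 months, and no outcome scale is listed at consent. The 2-week survey is therefore the only candidate. Family support is also first measured then; the article does not say which time point enters the model.

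**2. Order of events.**

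| Event | Timing in the text | Relative to first self-report |
|---|---|---|
| Envelope opened | At enrolment | Before |
| Arm disclosed | Immediately after consent | Before |
| Website access | 2 weeks after discharge | Not ordered |
| Set-up call | Accompanies access | Not ordered |

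Disclosure before the first self-report is certain on the text. Exposure before it is only possible.

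**3. The plan's own figure.** Sample Size gives a 2-point difference, effect size 0.44, alpha .05, 80% power and 81 per arm. The implied SD is 2 / 0.44 = 4.545. The two-sided normal formula 2 × ((1.960 + 0.842) / 0.44)² gives 81.08 per arm. Power at 81 per arm is 0.800 (normal) or 0.795 (t test). The figure reproduces, to rounding, as an unadjusted two-group comparison, and this point does not affect it.

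**4. Bias from a shifted baseline.** Let D be the true 12-month difference (intervention minus control; negative favours the intervention), b the shift that allocation or early use causes in the 2-week score, and s the common within-arm slope of the 12-month on the 2-week score. If b leaves no separate trace at 12 months, then

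adjusted difference = D − s × b.

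The documents give neither s nor b. Assuming |b| of 0.5 to 1.0 and s of 0.4 to 0.7, the estimate moves by 0.5 × 0.4 = 0.20 to 1.0 × 0.7 = 0.70 points. Against the 2-point target that is 0.20 / 2 = 10% to 0.70 / 2 = 35%. At b = 0 it is zero.

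**5. Consequences over an assumed grid.** SD is 4.545 at both times (so s equals the correlation), residual SD is 4.545 × √(1 − s²), and n is 81 per arm. The normal approximation is used, and any small loss of precision from baseline imbalance is ignored.

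| s | b | Adjusted difference if D = −2 | Power | Spurious difference if D = 0 | Two-sided type I error |
|---|---|---|---|---|---|
| 0.3 | 0 | −2.00 | 0.835 | 0 | 0.050 |
| 0.3 | −0.5 | −1.85 | 0.775 | +0.15 | 0.056 |
| 0.3 | −1 | −1.70 | 0.704 | +0.30 | 0.072 |
| 0.5 | 0 | −2.00 | 0.899 | 0 | 0.050 |
| 0.5 | −0.5 | −1.75 | 0.808 | +0.25 | 0.069 |
| 0.5 | −1 | −1.50 | 0.679 | +0.50 | 0.128 |
| 0.7 | 0 | −2.00 | 0.975 | 0 | 0.050 |
| 0.7 | −0.5 | −1.65 | 0.899 | +0.35 | 0.105 |
| 0.7 | −1 | −1.30 | 0.722 | +0.70 | 0.279 |

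A negative b (intervention arm better at 2 weeks) pulls the estimate towards no benefit. A positive b exaggerates benefit by the same amount.

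**6. If the shift persists.** Suppose b is a reporting shift still fully present at 12 months. The unadjusted difference is then D + b and the adjusted one is D + b × (1 − s). For b = 1.0 and s of 0.4 to 0.7, the unadjusted bias is 1.0 and the adjusted bias is 0.6 to 0.3. In that case adjustment reduces the bias.

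**The case against.** The strongest reply has four parts.

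- **Exposure is not shown.** Two events share the label of 2 weeks, which does not mean that access came first. The article is condensed, Figure 1 is not shown and may give an order, and such sequencing is often left to the full protocol. The home visit concerns people who could not use the site, so they had little exposure. This stands: a reader might infer that the website has contaminated the baseline, and the text supports only that it could. It does not answer the disclosure point, which the article states outright.
- **The size is assumed.** This also stands. The 10% to 35% is arithmetic on chosen inputs, and zero shift is equally compatible with the documents. Step 6 shows that adjustment can even help when the shift persists.
- **Dropout is addressed.** The plan specifies intention-to-treat analysis, multiple imputation under missing at random, and a comparison of those who withdraw with those who remain. Controls might leave after learning their arm and before any survey, but no differential loss is shown.
- **Changing enrolment mid-trial has a price.** Recruitment began in November 2018 and is under way, so later disclosure would create two enrolment regimes. This is a fair limit on the stronger remedy, but not on ordering survey before access.

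A reader might also infer that the QALY comparison is distorted through a baseline-utility adjustment. The article describes none. It says only that QALYs are calculated from the EQ-5D data, so that inference is not supported.

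**Conclusion.** The point holds in a limited form. On the stated sequence, the self-reported baseline covariates are post-randomization and unblinded. They may also be post-exposure for some participants, but that is not established. Adjusting for them can bias the 12-month difference in either direction, by an amount the documents do not determine and which is zero if the 2-week score does not shift. The 0.2 to 0.7 HADS points illustrates an assumed 0.5 to 1.0 point shift, an assumed slope of 0.4 to 0.7 and no persistence to 12 months; it is not an estimate for this trial. The sample size is unaffected. This is a worthwhile and cheap improvement to the primary analysis, not evidence that the trial's result will be wrong.

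**What to change.** - **All participants who have not reached 2 weeks.** Release the ICUTogether login, set-up call and home visit only once the 2-week survey is time-stamped as submitted, or after a fixed cut-off set in advance. Use the same reminders on the same timetable in both arms.
- **Patients still to be recruited, where feasible.** Open the envelope and disclose the arm only after the 2-week survey is returned. The website does not open before then, so the described intervention does not require disclosure on the ward.
- **Patients already enrolled.** Report survey and first-login dates. Add a sensitivity analysis of the primary outcome that omits the 2-week self-reported covariates and keeps those from the health record. By step 3, power without them stays close to the planned 80%. Because of step 6, it should be read beside the adjusted result, not as a replacement for it.
- **Reconcile the text on contact with controls.** Control Group allows only consent and surveys by post, while Data Collection and Measures has emailed surveys and telephone prompts for everyone. Identical reminders cannot be specified until these agree.

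**Cost.** A short amendment; slightly later access for late responders; some consenting patients who do not return the survey and so are not randomized (the documents give no figure); and enrolment procedures that differ before and after the amendment, which should be reported.

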### Randomization

Permuted block randomization will be conducted in blocks of 20 using a computer random number generator. Allocation concealment will be conducted by an independent researcher using sequentially numbered, opaque, sealed envelopes. The independent researcher will provide the researcher conducting the consent process with the sequentially numbered, sealed, opaque envelopes. Envelopes containing the treatment allocation will only be opened by the recruiting researcher on participant enrollment. Blinding of the participant to allocation status will not be possible owing to the nature of the intervention. The researchers conducting the data analysis will be blinded.

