## Results

Participant recruitment is currently underway. Recruitment is anticipated to be completed by December 2020 and the first results are expected to be submitted for publication in 2021.

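### One fixed, published block size of 20 in an open single-ICU trial lets a recruiter who keeps count know the last one or two allocations of most blocks beforehand.

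*Protocol article*

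**What the plan says.** The Randomization section of the protocol article fixes the scheme: "Permuted block randomization will be conducted in blocks of 20 using a computer random number generator". No second size or random variation of size is mentioned, and no stratification is described.

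On concealment, the same section says: "Allocation concealment will be conducted by an independent researcher using sequentially numbered, opaque, sealed envelopes". It continues: "The independent researcher will provide the researcher conducting the consent process with the sequentially numbered, sealed, opaque envelopes". On opening: "Envelopes containing the treatment allocation will only be opened by the recruiting researcher on participant enrollment".

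The allocation is open to participants and recruiter. The Participants section says "Participants will be informed which group they have been randomized to immediately after providing written informed consent", and the Randomization section adds "Blinding of the participant to allocation status will not be possible owing to the nature of the intervention". Only the data analysts are blinded.

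The Participants section describes a single general ICU at one hospital. The Results section says "Participant recruitment is currently underway", so the block size was in print while patients were still being enrolled.

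**The concern.** With a balanced block of known size, allocations already opened reveal those still sealed. Once ten patients in a block have gone to one arm, every remaining envelope in that block holds the other arm. Sealing gives no protection here, because the inference rests on envelopes that were properly opened.

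The person who can make the inference is the one who seeks consent. Some entry criteria leave room for judgement (ability to consent, ability to understand English), as does the effort put into an approach. If the next arm is known, a patient thought unlikely to use a website could be approached less keenly when the intervention is next, without anyone intending harm.

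This matters because participants know their group and the primary outcome, the HADS, is self-reported, so concealment up to the point of consent is a main protection against selection. The covariates in the Statistical Analysis section (baseline outcomes, age, gender, ICU stay, APACHE III score, family support) include no measure of motivation or confidence with devices. Blinded analysts cannot undo selection at entry.

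**Working it through.** **Inputs.** Block size 20 (Randomization). Total 162, 81 per arm (Sample Size), hence 1:1 allocation, taken as 10 + 10 in each block. The article gives no figure for predictability, so there is none to reproduce. The total of 162 serves only as an input. It reproduces closely enough: d = 0.44 with two-sided alpha .05 (sidedness is not stated, so this is assumed) needs 82 per arm by the normal approximation, and the t-test power at 81 per arm is 79.5%.

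**Assumptions.** The recruiter knows the block size, counts from the first patient and sees all earlier allocations.

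**Step 1: certain allocations per block.** For a block of 2n with n per arm, the expected number of places at the end that are already determined is 2n/(n + 1). With n = 10 this is 20/11 = 1.82, or 9.1% of the block.

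**Step 2: how they are spread.** P(at least k certain) = 2·C(20 − k, 10)/C(20, 10).

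| k | P(at least k certain) |
|---|---|
| 1 | 100% |
| 2 | 47% |
| 3 | 21% |
| 4 | 9% |

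Exactly one place is certain in 100 − 47 = 53% of blocks, and one or two in 100 − 21 = 79%.

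**Step 3: the whole trial.** 162 = 8 × 20 + 2. The two patients in the ninth block cannot be determined. The expected total is 8 × 20/11 = 14.5, and 14.5/162 = 9.0%. Simulation agrees (mean 14.5, 95% range 9 to 21).

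**Step 4: best guess.** Always guessing the arm with fewer patients so far gives n + (2^(2n)/C(2n, n) − 1)/2 correct guesses per block. With n = 10: 10 + (1,048,576/184,756 − 1)/2 = 10 + (5.675 − 1)/2 = 12.34 of 20, or 61.7%, against 50% by chance.

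**Step 5: other schemes.** For fixed sizes the formulas of Steps 1 and 4 apply. For varied sizes the figures are simulated at 162 patients, for a recruiter who knows the set of sizes but not their order.

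| Scheme | Certain allocations | Best guess correct |
|---|---|---|
| Fixed 4 | 33% | 71% |
| Fixed 10 | 17% | 65% |
| Fixed 20 (the plan) | 9% (14.5 of 162) | 62% |
| Varied 4/6/8 | 3.8 of 162 | 68% |
| Varied 16/20/24 | 1.5 of 162 | 61% |
| Varied, even sizes 12 to 28 | 0.1 to 0.2 of 162 across runs | 61% |

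Varying the size around 20 removes nearly all the certainty. It hardly changes the guess rate, which comes from balance itself.

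**Step 6: cost in balance.** With fixed blocks of 20 the final difference between arms is 0 or 2. With even sizes from 12 to 28 it is at most 4 in about 99% of simulated trials. At 83 against 79, the variance of a difference in means rises by the factor 81²/(83 × 79) = 6561/6557 = 1.0006.

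**The case against.** The strongest reply is that the article already describes sound concealment: a computer-generated sequence, an independent researcher, numbered opaque sealed envelopes, and opening tied to enrollment. Twenty is also a large block. About 91% of allocations are never certain, in 53% of blocks only the final place is, and a common alternative such as a fixed block of 4 would be far worse. The problem arises only if the recruiter keeps count of block boundaries, and no resulting shift in HADS can be estimated. The Intervention section also offers telephone guidance and a home visit to people who cannot use the site, which weakens the motive for selecting device-confident patients.

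Most of this stands, and it limits the size of the point. It does not answer it: the safeguards protect the unopened envelopes, while the inference comes from the opened ones.

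A reader might also infer that the whole stack of envelopes is handed over at once, or that nothing is recorded before an envelope is opened. The article says neither. It says only that the envelopes are provided to the consenting researcher, and a logging step is the kind of detail that a condensed article leaves to the full protocol. That the recruiter sees every past allocation assumes one recruiter, or several who share information; the number is not given. That the recruiter also chooses whom to approach is inferred from the role descriptions.

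**Conclusion.** The point holds in a narrow form. A single fixed block size, published during recruitment in an open single-ICU trial, makes about 1.8 allocations per block (about 14.5 of 162, or 9%) knowable with certainty before consent is sought. This rests on 10 + 10 blocks in one sequence, and on a recruiter who keeps count and knows all earlier allocations.

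A reader might conclude that concealment is absent, or that selection has taken place. The documents support neither: concealment is weakened at block ends, and nothing suggests that anyone has acted on a predicted allocation. The size of any bias cannot be derived from the article. This is an avoidable weakness with a cheap remedy.

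**What to change.** For the blocks still to be used, have the independent researcher generate a sequence whose block sizes vary at random around 20, for example even sizes from 12 to 28. Do not disclose the sizes to the recruiter, and do not publish them before enrollment ends. Do not move to smaller blocks.

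This cuts certain allocations from about 14.5 to about one or fewer per 162 patients. Blocks already used cannot be changed, so the gain is about 1.8 certain allocations for each block of 20 replaced; the article does not say how many remain. The best-guess rate stays at about 61%.

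The cost is a regenerated sequence and a new set of envelopes, plus a final arm difference usually of up to 4 patients instead of up to 2, with negligible loss of precision.

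Optionally, the independent researcher could keep the envelopes and release each one after the consented patient is logged. This guards against early or out-of-order opening, but it does not reduce guessing from past allocations. The short wait would not delay the intervention, because website access begins 2 weeks after hospital discharge; the statement that participants learn their group immediately after consent would need a small change.
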